### Interim analyses {21b}

No interim analyses are planned.

### Methods for additional analyses (e.g. subgroup analyses) {20b}

Sensitivity analyses will adjust for pre-specified baseline variables, such as risk group at baseline and whether recruitment occurred in person or via telehealth, in the regression models for the primary and secondary outcomes.

Sensitivity analyses are also planned to explore the impact on the intervention effect when using different data sources to define the primary outcome. For instance, defining risk-appropriate screening based on information from participant self-report and GP records on past screening at baseline (e.g. previous findings at colonoscopy, date of the last iFOBT). This is to emulate the real-world setting where the GP would not have access to additional administrative data during the consultation to determine what type of CRC screening was due (MBS, VAED). Sensitivity analyses will also test the robustness of the result to variations in the underlying assumptions and inputs to the health economic analysis.

Further additional analyses, including sensitivity, subgroup and supplementary analyses, will be described in a detailed statistical analysis plan (SAP) that will be made available prior to the analysis of the primary outcome.

### Methods in analysis to handle protocol non-adherence and any statistical methods to handle missing data {20c}

We will perform an adherence-adjusted analysis to account for non-compliance with uptake of the genomic test, as well as non-complete CRC risk result appointments, for the primary outcome [51, 55]. Appropriate methods for dealing with missing endpoint data will be undertaken, informed by a blinded review of the data. Details for the adherence-adjusted analyses and statistical methods to handle missing data will be provided in the SAP.

### Plans to give access to the full protocol, participant-level data and statistical code {31c}

Only researchers who require it will have access to the participant-level dataset stored in REDCap. All authors will have access to the full protocol. To assist with reproducible research, the statistical code will be made available to other researchers upon reasonable request.

## Oversight and monitoring

### Composition of the coordinating centre and trial steering committee {5d}

#### Coordinating centre

The coordinating centre will be responsible for the day-to-day running of the trial (SS, LB, MM, MK, SM, JMc and JE). The trial coordinator (SS) and chief investigator (JE) will oversee the running of the trial, including governance and administrative responsibilities (e.g. ethical approvals and maintenance of the protocol), identification and approach of general practices, GP and participant recruitment, data collection, verification and management, randomisation, delivery of the intervention and maintenance of the study budget. Additionally, the coordinating centre will organise steering committee meetings, draft study reports for the funding body and draft manuscripts.

#### Trial steering committee

A trial steering committee (SS, PC, SM, RDAL, MC, GF, JMa, CO, FW, DB, IW, JMc and JE) has been established to provide expert advice and oversight and ensure that the trial is conducted to the required standards. The steering committee includes the Chief Investigators, Associate Investigators and senior researchers from the coordinating centre. The steering committee is responsible for agreement of final protocol, protocol changes and reviewing progress throughout the study.

### Composition of the data monitoring committee, its role and reporting structure {21a}

This trial provides a personalised risk of CRC and screening recommendations to participants; any final decisions regarding CRC screening will be left to the participant in discussion with their GP. The intervention itself therefore is relatively low risk. This is a relatively small phase II efficacy trial. We do not expect significant adverse effects arising from the trial itself; there is no evidence that returning genomic risk results in substantial psychological distress [44]. We have therefore decided not to have a separate data monitoring committee. Oversight of the trial will be managed by the trial steering committee.

### Adverse event reporting and harms {22}

All protocol deviations will be recorded in the participant record and reported to the study coordinator and lead investigator (SS and JE), who will assess for seriousness.

Those deviations deemed to affect to a significant degree the rights of a trial participant or the reliability and robustness of the data generated in the clinical trial will be reported as serious breaches. Reporting will be done in a timely manner (within 72 h to the study coordinator and lead investigator) and within 7 days to the site’s Research Governance Office. The study coordinator and lead investigator must review and report serious breaches to the approving HREC within 7 days.

Where non-compliance significantly affects participant protection or reliability of results, a root cause analysis will be undertaken, and a corrective and preventative action plan prepared.

Where protocol deviations or serious breaches identify protocol-related issues, the protocol will be reviewed and, where indicated, amended.

### Frequency and plans for auditing trial conduct {23}

Researchers in the coordinating centre will meet at least weekly with the principal investigator to discuss and review trial progress. The principal investigator is contactable for prompt reporting of adverse events. The steering committee will meet quarterly, with more frequent meetings added as required throughout the duration of the trial set-up, recruitment and post-recruitment analysis phase. Minutes of all meetings will be digitally stored with all trial documentation. Progress will be reported to the trial funder every 12 months. There will be no independent auditing of trial conduct.

### Plans for communicating important protocol amendments to relevant parties (e.g. trial participants, ethical committees) {25}

This trial will be conducted in compliance with the current version of the protocol. Any change to the protocol document or informed consent form that affects the scientific intent, trial design and participant safety or may affect a participant’s willingness to continue participation in the trial is considered an amendment and therefore will be written and filed as an amendment to this protocol and/or informed consent form. All such amendments will be submitted to the HREC, for approval prior to being implemented.

### Dissemination plans {31a}

Data from this trial will be disseminated in several ways. Informal dissemination of results will occur with participants, participating GPs and other collaborators. Participants in the study are given the option at the time of consent to receive a plain language, one-page summary of the study findings after analysis is completed. Other collaborators will receive a similar summary, tailored to their position and interests (i.e. consumers will receive a lay summary).

Results of this research will be published in peer-reviewed journals. Additionally, the Primary Care Collaborative Cancer Clinical Trials Group (PC4) (who supports the study) facilitate communication and dissemination to a wide audience, including media releases to health professional and general outlets; Twitter and other social media outlets; PC4 Research Round-up and other health professional and general podcasts; and dissemination via the PC4 Consumer Advisory Group and their respective consumer networks. We will use all these approaches to promote the trial results. The chief investigators of the study hold primary responsibility for publications of results of the trial.

## Discussion

This trial aims to determine whether a personalised CRC risk estimate derived from a PRS with tailored screening recommendations and delivered in primary care increases risk-appropriate CRC screening. Precision cancer screening aims to recommend the most appropriate type and timing of screening based on risk but will not result in efficiency gains and reduction of mortality and morbidity from disease unless patients adhere to these recommendations.

Since the study began recruitment in April 2021 in Melbourne, Australia, our city has undergone several strict lockdowns due to the COVID-19 pandemic. Throughout the protocol described thus far, several contingencies have been outlined in our processes to reduce or remove the need for research staff to travel to general practices during recruitment. Some of these contingencies were planned before recruitment began, for example provisions for teletrial recruitment. Some, however, were proposed and implemented after recruitment began when lockdowns became lengthy, namely discussion of PRS results and screening recommendations for the intervention arm via teletrial rather than in person. All elements of this part of the intervention were replicated as closely as possible in the teletrial version, e.g. visually guiding participants through their PRS risk report using share screen facilities in teletrial software. This protocol amendment was discussed and approved by our trial steering committee including the trial statistician.

We considered carefully whether to employ a cluster randomised or individually randomised design for this trial. Cluster randomisation has the advantage of reducing the risk of contamination in the control arm but requires substantially larger sample sizes and may be subject to selection bias [56]. When clusters are of a moderate size and the risk of contamination is low, individual randomisation may be utilised [57]. Our previous individually randomised trial with a similar design, recruitment method and outcomes to this trial showed a low level of contamination (paper in submission). Consequently, we decided to randomise at an individual level in this trial.

A considerable point of discussion amongst the trial steering committee was the exclusion criteria for those who have at least one grandparent born in Africa. The scientific justification for this criterion is outlined above, as are the alternatives that we incorporated into the study protocol for those who met this exclusion criterion. There were several aspects that the steering committee considered when making this judgement. Firstly was the poorer accuracy of PRSs in those of African ancestry [30, 58]. Secondly was the ethical consideration that precision screening ultimately aims to increase equitable access to the best form of screening for an individual’s risk and providing access to a risk stratifying algorithm only for a portion of the population is likely to do the opposite. Thirdly was the already lower uptake of CRC screening for disadvantaged segments of the Australian population, including those who are culturally and linguistically diverse [17]. After careful consideration by the trial steering committee, we felt the risk of providing an inaccurate risk estimate to those of African ancestry was too great but were able to offer an alternative, more accurate phenotypic method of risk assessment to this group outside the trial, in collaboration with their GP.

The evidence behind PRSs to predict the risk of CRC is constantly growing [11, 59]. There are now approximately 100 SNPs associated with the risk of CRC [11]. These newer PRSs with more SNPs included show marginally better discrimination between cases and controls and ability to separate risk in population than those scores with fewer SNPs [8, 11]. As this evidence evolves, and newer PRSs become available with sufficient validation, as well as logistically available to be offered within the study, the study investigators may update the PRS in the study to be in line with the latest evidence for later participants. We believe this reflects likely future models of updating PRSs in clinical service; furthermore, given that the primary outcome is a behavioural one and not one based on cancer incidence, there are no methodological implications of using the most up-to-date PRS if feasible to do so.

Due to lengthy delays in approvals from Services Australia for the trial to include collection of MBS data from participants, the trial steering committee decided that recruitment should begin before this approval was granted. This resulted in the first study participants not providing written consent for the release of their MBS data at the time of recruitment. Approvals have now been granted from Services Australia and these initial participants are being recontacted for the purposes of this consent. However, this may result in some participants not being consented to access their MBS data (private colonoscopies and iFOBT kits ordered by GPs outside the NBCSP). The risk is that there may be screening events for some participants not captured in any other data source (GP records, VAED and NBCSP) which would alter the assessment of their primary outcome. However, in our experience of a previous trial using similar methods (paper in submission), there is sizeable overlap between information about colonoscopies and GP-ordered iFOBT captured in MBS, VAED and GP records. Therefore, we anticipate that the overall risk of bias in determining the primary outcome due to this issue is low.

This trial includes secondary outcomes that allow us to examine the effect of the intervention on behavioural predictors of CRC screening; this is particularly important should we not observe a clinically important difference in the proportion of risk-appropriate screening between arms. These secondary outcomes were selected from our pilot and development work of the intervention [39, 60], based on health behaviour theories [49, 61]. They include elements to determine whether participants’ attitudes towards screening were altered by the intervention, their perception of their own risk of CRC, the impact of risk prediction on their cancer worry and whether any non-adherence to screening recommendations can be attributed to GP behaviour rather than patient behaviour (e.g. if participants were not referred for discussion of colonoscopy or an iFOBT was not ordered by the GP, as determined by audit of GP records). These secondary outcomes will also provide valuable data to incorporate into a GP implementation strategy should the trial show a positive impact on risk-appropriate screening behaviour, allowing this strategy to focus on elements of the intervention that are proposed to have the greatest behavioural effect.

This study will test whether delivery of a CRC PRS in primary care is effective in encouraging risk-appropriate CRC screening compared to standard cancer risk reduction information in patients attending general practice. CRC population screening targeted using a PRS has the potential to not only recommend the most appropriate screening for an individual’s risk, but to encourage them to complete that screening. This would result in a cost-effective targeted screening programme, with the potential to reduce morbidity and mortality from CRC. If precision CRC screening is to be implemented across the population, we must determine how and where risk assessment will occur and whether the public are likely to accept and adhere to this new way of recommending screening. This study will provide valuable data regarding whether this could potentially be a cost-effective approach delivered in primary care, as the first point of health care provision for the vast majority of Australians.

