### Intervention description {11a}

The SCRIPT intervention is a ‘complex intervention’: that is, it contains several interacting components. The main component is a CRC PRS, with a post-test consultation to discuss the participant’s personal risk of CRC with an associated risk report for the participant and their GP. The reports are designed to encourage risk-appropriate screening and referral behaviours, based on the previous CRISP trial reports [36–38] and SCRIPT pilot work [39].

Participants will attend a consultation, within 1 week either side of their scheduled GP appointment, delivered by a trained research assistant either in person at their GP or via video call, where a brief discussion about the CRC PRS will take place. This will include information about the test and its potential implications, including potential impact on CRC screening recommendations.

A PRS will be generated from the presence or absence of each of the 45 SNPs, using the most up-to-date relative risks of CRC for each DNA variant and also the individual’s family history of CRC. For those who are of East Asian ancestry (e.g. Chinese, Japanese and Korean), there are sufficiently large GWAS studies for ancestry-specific relative risks for CRC for each of the 45 SNPs included in the PRS. Given this, these estimates will be used when calculating a PRS for those who self-identify as East Asian. For other ethnicities, there is evidence that European developed PRSs predict the risk of breast cancer in those of non-European ancestries [40] and in the absence of ancestry-specific PRSs, the European PRS estimates for CRC will be used.

Applying Australian age-sex incidence data to each individual’s PRS, a 10-year absolute risk of CRC will be calculated. Screening recommendations (iFOBT or colonoscopy) will be generated in accordance with the 2017 NHMRC-endorsed national guidelines which are based on 10-year absolute risks of CRC. Those with a 10-year risk of less than 1% are not recommended screening; those with a 10-year risk of 1% or greater and less than 4% will be recommended iFOBT; and those with a 10-year risk of 4% or greater will be recommended colonoscopic screening. However, within the study, no participant will be recommended less screening than the current NHMRC-endorsed national guidelines (for example, if a participant in their 50s has a PRS-derived 10-year risk <1%, they will still be recommended iFOBT screening).

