### Outcomes {12}

#### Primary outcome

The primary outcome is the difference between the two arms in the proportion of participants who have had risk-appropriate CRC screening at 12 months’ follow-up. The appropriate screening test in the intervention arm will be determined by the screening recommended according to their absolute 10-year risk of CRC derived from the PRS and family history. For those in the control arm, the appropriate screening test is determined by family history according to the NHMRC guidelines [5].

Risk-appropriateness of CRC screening was chosen as the primary outcome as previous cost-effectiveness studies have shown that CRC population screening targeted using a PRS would be cost-effective if the behavioural effect of returning the risk estimate increased screening by 5% [45]. Additionally, a study modelling the impact of various participation levels in the Australian NBCSP showed that increasing participation from 40 to 60% would result in 24,800 deaths prevented [3].

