## Data collection and management

### Plans for assessment and collection of outcomes {18a}

#### Primary outcome

The primary outcome is the proportion of participants who have had risk-appropriate CRC screening at 12 months’ follow-up. The appropriate type and frequency of screen will be determined by participant’s level of CRC risk as follows:

For those aged 50 years and over:*Average-risk category*: for participants whose 10-year absolute risk of colorectal cancer is less than 4% based on their PRS, family history, age and sex (intervention only) and who do not fall into the moderate risk category of the 2017 NHMRC-endorsed Australian guidelines [5] (both trial arms), iFOBT every 2 years is considered risk-appropriate screening.*Moderate-risk category*: for participants whose 10-year absolute risk of colorectal cancer is greater than or equal to 4% based on their PRS, family history, age and sex (intervention only), or they had a self-reported family history of CRC (both trial arms) that places then in the moderate risk category of the 2017 Australian guidelines [5], risk-appropriate screening is colonoscopy every 5 years.

For those aged under 50 years:*Average-risk category*: for participants whose 10-year absolute risk of colorectal cancer is less than 1% based on their PRS, family history, age and sex (intervention only) and do not fall into the moderate risk category of the 2017 NHMRC-endorsed Australian guidelines [25] (both trial arms), risk-appropriate screening is no screening until aged 50 years.*Moderate-risk category*: for participants whose 10-year absolute risk of colorectal cancer is greater than or equal to 1% based on their PRS, family history, age and sex (intervention only), or they had a self-reported family history of CRC (both trial arms) that placed then in the moderate risk category of the 2017 Australian guidelines [5], risk-appropriate screening is iFOBT every 2 years until aged 50 years.

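### Updating the PRS mid-trial does have methodological implications: PRS cut-points define success in the intervention arm only, so a new score can change the primary outcome in that arm

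*Protocol article*

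**What the plan says.** The test in use is a 45-SNP score. Intervention description {11a}: "A PRS will be generated from the presence or absence of each of the 45 SNPs". The Discussion then allows a replacement: once newer scores are validated and can be supplied, "the study investigators may update the PRS in the study to be in line with the latest evidence for later participants". It gives two reasons. Updating mirrors how scores would be revised in clinical service, and, since the outcome is behavioural and not cancer incidence, "there are no methodological implications of using the most up-to-date PRS if feasible to do so".

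The primary outcome is defined differently in the two arms (Outcomes {12}, Primary outcome). In the intervention arm the rule rests on a risk computed from the score together with family history: "The appropriate screening test in the intervention arm will be determined by the screening recommended according to their absolute 10-year risk of CRC derived from". Controls have a different rule: "For those in the control arm, the appropriate screening test is determined by family history according to the NHMRC guidelines".

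Plans for assessment and collection of outcomes {18a} gives the cut-points. From age 50, the average-risk category, for which iFOBT is the appropriate test, is "for participants whose 10-year absolute risk of colorectal cancer is less than 4% based on their PRS, family history, age and sex (intervention only"); at or above 4% the test is colonoscopy. Under 50, the moderate-risk category, for which iFOBT is appropriate, is reached when the "10-year absolute risk of colorectal cancer is greater than or equal to 1% based on their PRS, family history, age and sex (intervention only"); below 1% the appropriate behaviour is no screening.

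**The concern.** The stated reason does not support the conclusion. The outcome is behavioural, but which behaviour counts as a success depends on which side of 1% or 4% a person's PRS-derived risk falls. Two intervention participants with the same age, family history and screening record could be scored differently because they were assessed with different score versions. No score version affects how a control is scored. The Discussion itself says that newer scores separate risk in the population somewhat differently, so some reclassification should be expected.

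If the sentence stands, nobody has a reason to handle a score change as a design change, to log who had which version, or to check whether the result depends on it. The primary estimate would then average over two score versions, each with its own recommendations and its own effective success rule, and a reader could not separate them.

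**Working it through.** **Inputs, all from Sample size {14}.** 25% of the sample is aged 45–49, of whom 10% are moderate risk. Success at 45–49 is 95% in both arms if average risk; if moderate, it is 70% (intervention) and 10% (control). Success from age 50 is 60% and 40%. The planned contrast is 68% vs 51%, with 80% power, two-sided 5%, 5% missing and N = 274.

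**Reproducing the plan.**
- Intervention, 45–49: 0.90 × 0.95 + 0.10 × 0.70 = 0.925. Control: 0.90 × 0.95 + 0.10 × 0.10 = 0.865.
- Overall: 0.25 × 0.925 + 0.75 × 0.60 = 0.681; 0.25 × 0.865 + 0.75 × 0.40 = 0.516. The difference is 16.5 points, which the protocol gives as 17 (68% vs 51%).
- Two-proportion formula with pooled null variance, 0.68 vs 0.51: 130 per arm; 130 / 0.95 rounds up to 137; total 274. This matches.

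**Effect of reclassification at 45–49.** Let y be the share of the intervention band at or above 1%. The control rate stays at its planned value, because its rule does not use the PRS.
- Expected success in the band = 0.95(1 − y) + 0.70y = 0.95 − 0.25y.
- y = 0.10 gives 0.925; y = 0.20 gives 0.900. The fall is 2.5 points in the band and 0.25 × 2.5 = 0.6 points overall.
- With 130 evaluable per arm, the expected difference goes from 16.5 to 15.9 points and power from 78% to 74%, if everyone has the new score.
- If the new score puts fewer people above 1%, the sign reverses: y = 0.05 gives 16.8 points.
- If only a fraction f of participants has the new score, the overall shift is 0.6 × f. Protocol version 1.2 (14 February 2022) still describes the 45-SNP test, and recruitment was to run from April 2021 to October 2022. A switch at that date with even accrual (an assumption) gives f of about 8/18 = 0.44, so about 0.3 points.

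**Age 50 and over.** If an extra share h moves from iFOBT to colonoscopy with uptake q, and the others stay at 60%, the overall shift is 0.75 × h × (q − 0.60). The protocol gives neither h nor q. For an assumed h of 0.10:

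| Assumed colonoscopy uptake q | Overall shift, points |
|---|---|
| 20% | −3.0 |
| 40% | −1.5 |
| 60% | 0 |

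These also assume that everyone has the new score. They show only that the answer depends on a figure that is not in the document.

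**The case against.** The best defence is that the intervention is a PRS-based risk estimate with tailored advice, and that success means following the advice received. On that reading the verbal definition does not change with the version. The objective names no SNP count, and Intervention description {11a} already uses current relative risks and East Asian-specific ones, so there was never a single frozen score. The update is also optional and conditional, no switch is reported, and newer scores are described as discriminating only slightly better. Participants are never advised less screening than the national guidelines, and a history of adenomas or sessile serrated lesions overrides the PRS, so many people cannot be reclassified. Finally, the one-arm use of the PRS is in the base design and does not depend on an update.

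Most of this stands, and it limits the size of the problem. It does not rescue the sentence. Even as adherence to the advice received, the result mixes versions that send different people to different tests, with potentially different uptake. An update makes an existing one-arm definition vary over calendar time as well.

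A reader might also infer that a switch would confound the primary comparison with calendar time or lockdown-driven delivery. The document does not support that. Sequence generation {16a} has concurrent 1:1 allocation in permuted blocks within practice, so both arms span the same periods. Only a comparison between score versions would be confounded in that way, and the trial has no such objective.

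**Conclusion.** The claim that a score update carries no methodological implications is incorrect and should be removed. A new score can change what counts as success in the intervention arm and cannot do so in the control arm, so the primary estimate would become a mixture over versions. Comparability of the randomised arms is unaffected.

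Size and direction cannot be established from the document. The one illustration that uses the protocol's own success rates is about 0.6 points overall per 10 percentage points of 45–49-year-olds reclassified upwards; the 10-point step itself is assumed, and the shift is smaller for a late switch. It may be tempting to add a shift at 50 and over and say that about 3 of the planned 17 points are at risk. That would need an assumed reclassified share, an assumed colonoscopy uptake and every participant having the new score, and the restriction to later participants rules out the last of these.

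**What to change.** 1. In the Discussion, delete the statement. Say instead that a score change can alter the recommendation, and hence the success rule, in the intervention arm.
2. Treat any PRS change as an amendment affecting trial design, under the section on communicating protocol amendments {25}.
3. Record the PRS version for each participant and the date of any switch. Define the switch by randomisation date, because controls are scored without a PRS and have no version of their own.
4. State that each intervention participant is scored against the recommendation actually issued.
5. Pre-specify two sensitivity analyses of the primary outcome: (a) participants in both arms randomised before the switch, which remains a randomised comparison under one version; (b) both arms scored by one common rule, either the national guidelines for both or one PRS version for both. The second form of (b) is feasible in principle because Trial design {8} has DNA collected from everyone at baseline. It requires control samples to be genotyped for the SNPs that version uses.

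Keeping one version until the last randomisation is an option for the investigators, not a required change. It would simplify the analysis, but it runs against their stated reason for allowing updates. The cost of the fix is one paragraph, the version and switch-date record, and a little extra analysis.
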